# Comparing adherence to MDR-TB treatment among patients on self-administered therapy and those on directly observed therapy: non-inferiority randomized controlled trial

**DOI:** 10.1186/s13063-023-07314-z

**Published:** 2023-05-12

**Keywords:** Multi-drug-resistant tuberculosis, Medication events monitoring system technology, Directly observed therapy, Differentiated care, TB treatment adherence, TB treatment outcomes, Resource-limited settings, Sub-Saharan Africa, TB drug PK levels

## Abstract

**Background:**

Adherence is key to the treatment success of multi-drug resistant tuberculosis (MDR-TB) and prevention of community transmission. Directly observed therapy (DOT) is the recommended approach for the management of patients with MDR-TB. Uganda implements a health facility-based DOT approach where all patients diagnosed with MDR-TB report to the nearest private or public health facility for daily observation of ingesting their medicines by a health care provider. Directly observed therapy is very costly for both the patient and health care system. It follows the assumption that MDR TB patients have a history of poor adherence to TB treatment. But only 21% of MDR-TB patients notified globally and 1.4–12% notified in Uganda had been previously treated for TB. The shift to all oral treatment regimen for MDR-TB provides an opportunity for the exploration of self-administered therapy for this group of patients even with use of remotely operated adherence technology. We are conducting a non-inferiority open-label randomized controlled trial to compare adherence to MDR-TB treatment among patients on self-administered therapy (measured by Medication Events Monitoring System (MEMS) technology) with a control group on DOT.

**Methods:**

We plan to enrol 164 newly diagnosed MDR-TB patients aged ≥ 8 years from three regional hospitals based in rural and urban Uganda. Patients with conditions that affect their dexterity and ability to operate the MEMS-operated medicine equipment will not be eligible to participate in the trial. Patients are randomized to either of the two study arms: self-administered therapy with adherence being monitored using MEMS technology (intervention arm) or health facility-based DOT (control arm) and will be followed up monthly. Adherence is measured by the number of days the medicine bottle is open to access medication as recorded by the MEMS software in the intervention arm and treatment complaint days as recorded in the TB treatment card in the control arm. The primary outcome is the comparison of adherence rates between the two study arms.

**Discussion:**

The evaluation of self-administered therapy for patients with MDR-TB is important to inform cost-effective management strategies for these patients. The approval of all oral regimens for the treatment of MDR-TB provides an opportunity for innovations such as MEMS technology to support sustainable options for MDR-TB treatment adherence support in low-resource settings.

**Trial registration:**

Pan African Clinical Trials Registry, Cochrane #PACTR202205876377808. Retrospectively registered on 13 May 2022

**Supplementary Information:**

The online version contains supplementary material available at 10.1186/s13063-023-07314-z.

In an effort to counter the effects of non-adherence, including poor treatment outcomes and transmission of resistance strains, directly observed therapy (DOT) was adopted as a strategy, where patients are observed as they take their daily dose by either a community health care worker, family member or health care worker. The observation may occur at a health facility when the patient reports for their daily dose or may entail the health provider visiting the patient at their home premise. Uganda implements a health facility-based DOT approach where all patients diagnosed with MDR-TB report to the nearest private or public health facility for DOT. Although treatment success rates on patients treated using the DOT strategy in Uganda have gradually improved from 70.6% in 2018 to 77.9% in 2020, these rates are still below the 90% target set by the WHO. Factors that contribute to low treatment success rates with DOT include lack of financial resources to make daily clinic visits, poor road infrastructure, long distances to nearest health facility, insufficient and overworked health care workers, and overburdened facilities [6, 7]. Therefore, innovations that can support remote monitoring of MDR-TB treatment should be explored to reduce time and financial costs. A systematic review on strategies to improve adherence to MDR-TB treatment demonstrated that community DOT had varied effectiveness and that barriers to achieving adherence are patient-based; there is therefore a need to develop personalized interventions [8].

The Medication Events Monitoring System (MEMS) (AARDEX®) is a portable smart medication device designed to monitor treatment adherence by transmitting electronic information on the number of times the medicine cap is opened, specifying dates and times. This information is taken to correlate with actual times that patients ingest their medication and can be used to validate the accuracy of self-reported adherence. The device is operated by a long-lasting battery and is able to transmit software information in real time and store information for many months following battery outage. The information on patient non-adherence as captured by MEMS technology has been shown to accurately correlate with treatment outcomes among people living with HIV [9]. In addition, the device has also shown to outperform self-report or pill counts and is acceptable to patients who found it easy to open and carry it on their person [9, 10].

We plan to conduct an open-label randomized non-inferiority clinical trial among patients receiving MDR-TB treatment in Uganda to compare adherence rates among those using self-administered therapy with MEMS technology vs DOT, which is the current standard of care in Uganda for MDR-TB. We will correlate adherence information with serum drug concentrations and compare determined treatment outcomes between the two groups.

## Explanation for choice of comparators

For the purposes of this study, we shall be using patients on standard of care (DOT), as the comparator group. This comprises patients with MDR-TB who have to report daily to a DOTS facility to be observed as they ingest their medication. DOT is the standard of care for MDR-TB patients and presently the only alternative for patient follow-up.

## Specific objectives

The primary objective of the study is to determine if adherence to MDR-TB treatment among patients on self-administered therapy (measured by MEMS technology) is non-inferior to that among patients on directly observed therapy (DOT). The secondary objectives of the study include determining the correlation between MDR-TB drug serum concentrations and adherence as measured by MEMS technology and comparing treatment outcomes between MDR-TB patients on self-administered therapy and standard DOT

## Trial design

This study will be conducted as a multi-centre open-label randomized clinical trial with two parallel arms and 1:1 enrolment ratio (82 patients in the intervention arm and 82 controls). We shall enrol a total of 164 participants newly diagnosed with pulmonary MDR-TB or rifampicin-resistant TB (RR-TB) from 3 TB tertiary care centres from 2 regions of the country.

### Methods

We used the SPIRIT reporting guidelines in reporting our study methods [11].

#### Study setting

This study will be conducted in Mulago National Referral Hospital in the central region and Lira regional referral hospital in the northern region. These hospitals register the highest number of MDR-TB patients in Uganda. Both these hospitals are public government hospitals not for profit. The hospitals house specialized TB wards and clinics, operating a weekly TB clinic to follow up patients with drug-sensitive and drug-resistant TB on therapy and to initiate therapy for newly diagnosed patients. Being referral hospitals, these facilities receive patients referred from health facilities within a radius of up to 30km and in some cases even further.

#### Diagnosis and management of MDR-TB

Diagnosis of MDR-TB is based on Gene Xpert® testing of sputum for identification of resistance to rifampicin (RR-TB) followed by culture and drug susceptibility testing (DST) for phenotypic characterization; however, treatment is started prior to the receipt of culture and sensitivity results due to long turnaround time of 10–16 weeks. Treatment options for MDR-TB/RR-TB currently include:Category 1—A bedaquiline-based injection-shorter treatment regimen (STR) (9 to 12 months) reserved for MDR-TB/RR-TB patients who have not been previously treated with second-line drugs and in whom resistance to fluoroquinolones and second-line injectable agents has been excluded. Drug options for shorter treatment regimen include an intensive phase of 4 months (extended to 6 months in case of delayed sputum smear conversion) containing high-dose gatifloxacin or moxifloxacin, kanamycin, prothionamide, clofazimine, high-dose isoniazid, pyrazinamide, and ethambutol followed by a continuation phase of 5 months containing gatifloxacin or moxifloxacin, clofazimine, ethambutol and pyrazinamide [12].Category 2—The longer treatment regimens (18 to 20 months) based on core backbone agents but individualized depending on age, fluoroquinolone resistance, and site of disease.

According to standard of care, patients with MDR-TB are managed as in-patients at central MDR treatment facilities (which include Mulago and Lira hospitals) in the intensive phase of treatment after which they are discharged and required to report to the central MDR treatment facility monthly for review and drug refills. Following discharge, during the continuation phase, patients are required to report daily to the nearest private or public facility registered under DOT programme [13]. Monthly reviews during routine care include safety laboratory investigations including a full blood count, liver and renal function tests, sputum culture, DST and adherence counseling.

#### Eligibility criteria

We shall enrol consented patients with newly diagnosed pulmonary MDR-TB and RR-TB patients aged ≥8 years, initiated on oral MDR-TB therapy (category 1 or 2). Patients with any condition that inhibits the use of the MEMS device, e.g. dexterity or debilitating arthritis, will be excluded from participation.

#### Intervention arm

For this trial, we shall use two kinds of MEMS-operated devices, the MEMS cap and the MEMS Electronic DosePak® (EDP). At enrolment, patients on the self-administering arm will be provided with both devices; the MEMS cap will be placed over a medicine bottle containing bedaquiline. The concomitant medication will be packaged in a convenient pack containing all tablets to be swallowed each day and placed into the medication box with the EDP® technology Patients will be instructed on how to use the MEMS devices. Each time a patient opens up the cap over the bedaquiline bottle or the lid of the medicine box, the time and date of this event will be immediately captured. Adherence data from the MEMS devices will be downloaded by the study team every month during the routine visits. The devices will provide information on specific calendar dates and times when the devices were opened. Information on the calendar days with event markings to signify the date and time when medication containers were opened will be displayed on a computer. The software will contain two separate input calendars for both the MEMS cap and the EDP box for each participant. This same adherence data will be shared with primary clinician and used to tailor adherence counselling given to patients, exploring patterns of missed medication and brainstorming for solutions with the patient (Table 1).

**Table 1 Tab1:** Description of study arms

**Control: DOT**	**Intervention: self-administered therapy with MEMS technology**
Patients report daily to the nearest health unit to be observed by a health care provider as they ingest their medication Behavioural: Adherence counselling. Patients will receive adherence counselling as scheduled by their primary care health providers	Device: MEMS CAP without LCD display and EDP® technology on medicine box. Standard MEMS devices record the time and date when the bottle is opened The MEMS technology automatically complies drug dosing history information by electronically recording the date and time of each opening of the medication cap and or box Behavioural: Adherence counselling. Patients will receive adherence counselling as scheduled by their primary care health providers

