### Statistical: outcomes

#### Adherence assessment

The primary outcome is the overall adherence rates among MDR-TB patients on self-administered therapy and on DOT. For the participants on the intervention arm, opening of the devices will be equated to a patient swallowing their medication and adherence will be derived from the number of days the device was opened as a proportion of the total number of days in the entire period of their MDR-TB treatment. Patients on the intervention arm will be required to take no less than 70% of their medication to be considered as having good adherence. For participants on the control arm (DOT), adherence information will be obtained from their TB treatment cards. Adherence rates will be calculated from the number of days that they report to the DOTS facility as a proportion of the total number of treatment complaint days in the entire period of their MDR-TB treatment. Participants who take their medication at least 80% of the time (missing no more than 5 days each month) will be considered as having good adherence.

The primary analysis will be a comparison of overall adherence in each arm. Adherence by self-administration (proportion of expected openings of the MEMS devices) and DOT (proportion of DOT visits) will also be compared at 2 months and 6 months in the intervention and control arms. The chi-square test and 1-way analysis of variance models will be used to compare outcomes by randomization arm. We shall use independent samples *t*-test to test for statistical difference mean adherence rates in the patient in the intervention and control arms. We will use an intent-to-treat approach (analysed all participants regardless of drug refills) to compare adherence outcomes by randomization arm using a generalized estimating equations model using repeated measures with identity link, exchangeable correlation structure and robust variance estimates.

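### The intervention-arm primary endpoint is worded inconsistently for a two-device arm, and no rule says which opening makes a day adherent

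*Protocol article*

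**What the plan says.** All references are to the protocol article.

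- **Intervention arm.** At enrolment each patient receives two devices. For the first, "the MEMS cap will be placed over a medicine bottle containing bedaquiline". The second is a box that holds the other medicines, packed by day. On the data, "The software will contain two separate input calendars for both the MEMS cap and the EDP box for each participant". Both are downloaded monthly.
- **Abstract, Methods.** "Adherence is measured by the number of days the medicine bottle is open to access medication as recorded by the MEMS software". Read with the Intervention arm section, the bottle holds one drug of the regimen.
- **Adherence assessment, primary outcome.** In one sentence, "opening of the devices will be equated to a patient swallowing their medication", in the plural, and then "adherence will be derived from the number of days the device was opened as a proportion of the total number of days" in the treatment period, in the singular.
- **Adherence assessment, 2- and 6-month comparisons.** The measure is the "proportion of expected openings of the MEMS devices": plural again, and with expected openings in place of all treatment days.
- **Table 1 and Adherence to interventions.** Table 1 speaks of openings of the cap and/or the box. The other section says the software is read for use of the cap and the box.
- **Control arm and Adherence assessment.** The card is ticked for each day the patient visits the facility. The rate is reporting days over what the text calls treatment complaint days (presumably compliant days), which is a third wording for a denominator.
- **Sample size.** Non-inferiority requires the lower 95% limit of MEMS minus DOT to lie above −10%.

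**The concern.** The primary endpoint in the intervention arm cannot be computed in a unique way from the text. The stated rules differ in the numerator (bottle, device, devices) and in the denominator (all treatment days, expected openings). A count based on one container, or on either, credits a full day when the rest of the regimen may not have been accessed.

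The denominator matters too. The article does not say on which days a bedaquiline dose is due, and it describes the longer regimens as individualized. If some treatment days carry no bedaquiline dose, a bottle count over all treatment days scores those days as missed in a patient who took everything prescribed.

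The choice affects one arm only, so any shift in that arm's mean adherence passes one for one into the difference tested against the margin. The Blinding section says that the study team and the data manager are unblinded. An unfixed rule therefore leaves room for a choice made after the data are seen.

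**Working it through.** **Plan's own figure.** There is none to reproduce. The article gives no expected rate of disagreement between cap and box. The inputs it does give are the −10-point margin, the assumed MEMS adherence of at least 70% (Sample size), the 70% cut-off for good adherence in the intervention arm (Adherence assessment), and treatment of about 9 or 18 months.

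**Step 1: order of the rules.** Take one common set of days. Days with both devices opened are a subset of days with a given device opened, and these are a subset of days with at least one opened. Hence either ≥ single ≥ both. This needs no assumption.

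**Step 2: the gap.** Either minus both is the share of days with exactly one device opened. It is 10 points or more exactly when that share is 10% or more. At an assumed 30 days a month, this is 0.10 × 30 = 3 days a month, 27 of 270 days (9 months) or 54 of 540 days (18 months).

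**Step 3: range.** Assume both devices have the same daily opening rate p and within-day correlation ρ.

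- either = p + p(1−p)(1−ρ)
- both = p − p(1−p)(1−ρ)
- either − both = 2p(1−p)(1−ρ)
- single against a combined rule = p(1−p)(1−ρ), half of that

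For p = 0.85, p(1−p) = 0.1275:

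- ρ = 0: 97.8% against 72.3%, gap 25.5 points
- ρ = 0.5: 91.4% against 78.6%, gap 12.8 points
- ρ = 0.9: 86.3% against 83.7%, gap 2.6 points

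Either-minus-both gap in points, and the largest ρ at which it still reaches 10, that is 1 − 0.10/[2p(1−p)]:

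| p | ρ = 0 | ρ = 0.5 | ρ = 0.9 | Largest ρ for 10 points |
|---|---|---|---|---|
| 0.70 | 42.0 | 21.0 | 4.2 | 0.76 |
| 0.80 | 32.0 | 16.0 | 3.2 | 0.69 |
| 0.85 | 25.5 | 12.8 | 2.6 | 0.61 |
| 0.90 | 18.0 | 9.0 | 1.8 | 0.44 |
| 0.95 | 9.5 | 4.8 | 1.0 | none at ρ ≥ 0 |

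At ρ = 1 every gap is 0. Single against combined at p = 0.85 is 12.8, 6.4 and 1.3 points. Bottle-only against box-only differs by 0 if the two opening rates are equal, and otherwise by the difference in those rates.

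**Step 4: share of patients above the cut-off (illustration only).** Suppose patients' opening rates follow a beta distribution with mean 0.80 and parameters summing to 10. The share at or above 70% is then 94.5% (either), 80.4% (single) and 60.9% (both) at ρ = 0.5, and 84.0%, 80.4% and 76.6% at ρ = 0.9.

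**The case against.** Several points can fairly be made for the plan.

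- **The abstract may be shorthand.** Table 1 also uses the bottle loosely and follows it at once with cap and/or box, and the statistical section uses the plural twice. This makes a deliberate one-drug endpoint less likely. It does not remove the conflict, because no section says what the plural means for a day on which only one device was opened.
- **Combining two calendars is analysis-plan detail.** A condensed article may leave the derivation to a document not shown. That would answer silence. Here the article does state measures, and they disagree with each other whatever another document says.
- **Either against both compares two rules that the text does not state.** This stands. The conflict actually written is the bottle against the device or devices. For single against combined, the gaps are half as large.
- **Agreement may be close.** Both containers hold the same patient's daily medicines. At ρ = 0.9 the gap is 1.8 to 4.2 points for p from 0.70 to 0.90. This also stands.

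Four stronger readings are tempting, and the article does not support them. A reader might count the two-calendar sentence as a third definition, but it describes data capture. A reader might conclude that the choice does move the result past the margin, or lets the team obtain either verdict, but that needs a disagreement rate that is not given. A reader might supply a bedaquiline schedule and compute the score of a perfectly adherent patient, but the article states no schedule. Lastly, a reader might say that only a both-containers rule matches DOT. The card is ticked for a visit at which intake is observed, and nothing says that a tick verifies every drug.

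**Conclusion.** The concern holds as an inconsistency in the definition of the primary endpoint. Numerator and denominator are worded differently between the abstract and the statistical section, and within the latter, for an arm with two separately logged containers. No rule says which opening makes a day adherent.

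The ordering of the rules is certain. The size is conditional: the choice could move intervention-arm adherence by the 10-point margin or more if at least 10% of days have exactly one device opened. The range in the table rests on equal opening rates for the two devices and on an assumed correlation. It runs from no effect under perfect agreement to 42 points at p = 0.70 with independent openings, and it stays below 10 points at p = 0.95 for any correlation of zero or more.

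**What to change.** Before adherence is compared by arm, at any interim look as well as at the end, reconcile the abstract, the Intervention arm section and Adherence assessment to one rule:

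- A day is adherent when every container with a dose due that day was opened that day.
- The denominator is the number of days on which that patient had a dose prescribed.
- The control arm uses the same prescribed-days denominator in place of treatment complaint days.
- Cap-only, box-only and either-device versions are reported as sensitivity analyses, together with the observed share of days with exactly one device opened. That share shows directly how much the choice matters.

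This is a measurement rule and changes nothing in treatment. The cost is wording and programming, since both devices are already downloaded every month, plus a record of the days on which each container had a dose due. The downside is that measured adherence in the intervention arm will be somewhat lower than under an either-device rule.

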## Interventions: modifications

Participants may withdraw from the study at any time at their own request, or they may be withdrawn at any time at the discretion of the investigator or sponsor for safety or behavioural reasons, or the inability of the subject to comply with the protocol required schedule of study visits or procedures. Patients who are withdrawn at any time of the study may be replaced.

